
| hepatitis C treatment. Historical medical record or testing to ensure a negative viral load may be permitted during the Screening Period. HCV ribonucleic acid will be tested in all subjects, including subjects with a history of treated HCV infection or with positive HCV antibody at Screening, provided that a negative hepatitis C viral load has not been documented at ≥12 weeks after the cessation of hepatitis C treatment.   1. A female subject must meet any one of the following criteria: a. Surgically sterile    1. Postmenopausal with ≥12 months of amenorrhea without an alternate medical cause    2. Follicle-stimulating hormone level consistent with postmenopausal state if amenorrheic for <12 months or if <55 years of age    3. If a subject is of childbearing potential, must have a negative serum pregnancy test during Screening and agree to abstain from sexual activity or agree to use a highly effective form of birth control (failure rate <1% per year) for the duration of the study and for at least 30 days after the last dose of study drug 2. A male subject must meet the following criteria:    1. Male subjects with a partner who is a female of childbearing potential (FCBP), must agree to abstain from sexual activity or agree to use a highly effective form of birth control (failure rate <1% per year) for the duration of the study and for at least 90 days after the last dose of study drug. Note: Female partner use of a highly effective form of birth control (failure rate <1%) is acceptable for male subjects participating in the study.    2. Male subjects capable of fathering a child must agree to refrain from sperm donation for the duration of the study and for at least 90 days after the last dose of study drug. 3. A subject must agree to refrain from physical activity outside of normal activities of daily living before Day 1 and for the duration of the study. 4. A baseline CFQ-11 Total score (by Bimodal Scoring) of _≥8._     **Exclusion Criteria (Cohort A and B)**  A subject will be excluded from the study if **any** of the following criteria are met:   1. Other than PASC, have an explanation for fatigue. This includes but not limited to hypothyroidism; chronic cardiovascular, neurological, endocrinological, or peripheral vascular disease; history of major depression; clinically significant anemia; chronic liver disease; rheumatologic diseases requiring treatment with steroids or immunosuppressants; or other cause of neuromuscular disease such as muscular dystrophy. 2. Other than PASC, a history or presence of an uncontrolled, clinically significant disease including:    - Type 1 or Type 2 diabetes mellitus    - A medical condition that may interfere with absorption of the study drug, including but not limited to resection of any part of the gastrointestinal tract, gastric or intestinal bypass, any bariatric surgery, or inflammatory bowel disease |

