###### Cohort A Only

• an elevated PCr recovery rate constant following moderate exercise on 31P-MRS (τ_PCr_ ≥50 seconds); and

Note: Documented 31P-MRS within 3 months of Screening and after 3 months of acute COVID-19 infection is acceptable. If a historical 31P-MRS has been used to determine eligibility, then 31P-MRS should be repeated within 1 month prior to Day 1 (ie, during the Screening Period) to confirm eligibility and establish baseline.

1. Other than PASC, a subject must be in good health without other significant medical or not well controlled medical or psychiatric conditions. Allowable conditions include mild hypertension,

dyslipidemia, pre-diabetes defined as HbA1c ≤ 6.0%, and/or asthma (mild and not requiring chronic daily treatment). Subjects who are treated for these conditions must be well controlled on a stable regimen (lifestyle modifications and/or medications), for at least 3 months prior to Screening and anticipate no significant alterations to these regimens for the duration of the study. However, doses of certain medications (eg, statins, antihypertensives) used to treat stable chronic conditions may be modified during the study for safety or tolerability issues, if needed at the discretion of the Principal Investigator (PI).

Note: A history of treated hepatitis C virus (HCV) infection is allowed, provided that a negative hepatitis C viral load has been documented at ≥12 weeks after the cessation of hepatitis C treatment. Historical medical record or testing to ensure a negative viral load may be permitted during the Screening Period. HCV ribonucleic acid will be tested in all subjects, including subjects with a history of treated HCV infection or with positive HCV antibody at Screening, provided that a negative hepatitis C viral load has not been documented at ≥12 weeks after the cessation of hepatitis C treatment.

1. A female subject must meet any one of the following criteria:
   1. Surgically sterile
   2. Postmenopausal with ≥12 months of amenorrhea without an alternate medical cause
   3. Follicle-stimulating hormone (FSH) level consistent with postmenopausal state if amenorrheic for <12 months or if <55 years of age

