   4. If a subject is of childbearing potential, must have a negative serum pregnancy test during Screening and agree to abstain from sexual activity or agree to use a highly effective form of birth control (failure rate <1% per year) for the duration of the study and for at least 30 days after the last dose of study drug
2. A male subject must meet the following criteria:
   1. Male subjects with a partner who is a female of childbearing potential (FCBP), must agree to abstain from sexual activity or agree to use a highly effective form of birth control (failure rate <1% per year) for the duration of the study and for at least 90 days after the last dose of study drug. Note: Female partner use of a highly effective form of birth control (failure rate <1%) is acceptable for male subjects participating in the study.
   2. Male subjects capable of fathering a child must agree to refrain from sperm donation for the duration of the study and for at least 90 days after the last dose of study drug.
3. A subject must agree to refrain from physical activity outside of normal activities of daily living before Day 1 and for the duration of the study
4. A baseline CFQ-11 total fatigue score (by Bimodal Scoring) of ≥8.

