## 5.3 Prevention of Pregnancy

Subjects who are FCBP or males with a partner who is a FCBP must use a highly effective form of birth control from the day of the first dose of study drug, throughout the study, and for 30 days (females) or 90 days (males) after the last dose of study drug.

Definition of Female of Childbearing Potential and of Fertile Men

A female is considered of childbearing potential (ie, fertile) following menarche and until becoming post-menopausal unless permanently sterile. Permanent sterilization methods include hysterectomy, bilateral salpingectomy, and bilateral oophorectomy.

A postmenopausal state is defined as no menses for 12 months without an alternative medical cause. A high FSH level in the postmenopausal range may be used to confirm a postmenopausal state in women not using hormonal contraception or hormonal replacement therapy. However, in the absence of 12 months of amenorrhea, a single FSH measurement is insufficient.

A man is considered fertile after puberty unless permanently sterile by bilateral orchidectomy Birth Control Methods Which May be Considered as Highly Effective

A highly effective method is one that can achieve a failure rate of <1% per year when used consistently and correctly. The acceptable birth control methods for female subjects are:

- Combined (estrogen and progesterone- [progestogen-] containing) hormonal contraception associated with inhibition of ovulation, administered by oral, intravaginal, or transdermal routes;
- Progesterone- (progestogen-) only hormonal contraception associated with inhibition of ovulation, administered by oral, injectable, or implantable routes;
- Intrauterine device;
- Intrauterine hormone-releasing system;
- Bilateral tube occlusion;
- Vasectomized partner (provided the partner is the sole sexual partner of the FCBP subject and that the vasectomized partner has received medical assessment of the surgical success); or
- Complete sexual abstinence (ie, refraining from heterosexual intercourse; the reliability of sexual abstinence should be evaluated in relation to the duration of this study and the preferred and usual lifestyle of the subject).

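### Section 4.1 and the synopsis admit a woman with under 12 months of amenorrhea on an FSH level alone, a standard that Section 5.3 rejects; the practical risk is small

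*Protocol*

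**What the plan says.** **Entry rule.** Section 4.1 introduces the options for women with "A female subject must meet any one of the following criteria". There are four: surgical sterility, postmenopausal status with at least 12 months of amenorrhea, an FSH route, and a route for women of childbearing potential (FCBP). The FSH route, option 3, reads "Follicle-stimulating hormone (FSH) level consistent with postmenopausal state if amenorrheic for <12 months or if <55 years of age". The synopsis has the same list and the same option: "Follicle-stimulating hormone level consistent with postmenopausal state if amenorrheic for <12 months or if <55 years of age". Option 4 begins "If a subject is of childbearing potential, must have a negative serum pregnancy test during Screening and agree to abstain from sexual activity" and offers highly effective contraception as the alternative to abstinence.

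**Definitions.** Section 5.3 holds the protocol's only definition of FCBP: "A female is considered of childbearing potential (ie, fertile) following menarche and until becoming post-menopausal unless permanently sterile". It continues: "A postmenopausal state is defined as no menses for 12 months without an alternative medical cause". A high FSH level, it says, "may be used to confirm a postmenopausal state in women not using hormonal contraception or hormonal replacement therapy". It closes the point with "in the absence of 12 months of amenorrhea, a single FSH measurement is insufficient".

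**Laboratory lists.** FSH appears only among the Screening laboratories in Appendices 3 and 4. Its footnote there covers women under 55 and women with under 12 months of amenorrhea, the same groups that option 3 names.

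**The concern.** Two sections give a site different answers about the same woman. By the entry list she qualifies on hormone evidence. By Section 5.3 that evidence does not establish that she is postmenopausal, so she remains FCBP. Because the options are alternatives, qualifying by option 3 means that the conditions written into option 4 are not applied to her as entry conditions.

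What could be lost is the explicit contraception agreement and the negative serum test as stated conditions of entry. A site might go further and reason that a woman admitted on a postmenopausal-range FSH is not FCBP. It could then also place her outside the appendix footnotes that limit the serum and urine pregnancy tests to FCBP. The trial takes women from 18 to under 65, so perimenopausal women are eligible by age.

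**Working it through.** The question is one of textual consistency, and the plan has no figure to reproduce. Take a woman with 8 months of amenorrhea (an illustrative value), not sterilized, with one FSH result in the postmenopausal range at Screening.

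| Step | Text applied | Result |
|---|---|---|
| Does she satisfy an entry option? | Section 4.1 and synopsis, option 3 | Yes: amenorrhea is under 12 months and FSH is in range |
| Is one option enough? | Lead-in to the list | Yes |
| Is she postmenopausal? | Section 5.3 | No: 8 is less than 12 months |
| Does the FSH result change that? | Section 5.3 | No: one value does not suffice without the 12 months |
| Is she FCBP? | Section 5.3 | Yes: neither postmenopausal nor permanently sterile |
| Must she meet option 4 to enter? | Section 4.1, read literally | No: option 3 has already been met |

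**Could a second FSH value reconcile the two sections?** Nothing requires one. Section 6.6.4.1 and the synopsis permit a single retest at the investigator's discretion, and they word it for the exclusion criteria, whereas FSH serves an inclusion criterion. A Cohort A screen failure who is rescreened for Cohort B may have FSH drawn again, but no text says how the two values would be combined. Option 3 also lacks Section 5.3's limit to women not taking hormones.

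**What still protects her if Section 5.3 is applied?**

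- Section 5.3 requires highly effective contraception of every FCBP subject, whichever option admitted her. The period is 28 dosing days + 30 days after the last dose = 58 days.
- Inclusion criterion 2 requires every subject to be willing to comply with the protocol's requirements, which include Section 5.3.
- Section 6.6.4.4 states 1 serum test at Screening + 1 urine test at Baseline + 1 urine test at end of treatment or early termination = 3 tests, with no FCBP limit.
- The pregnancy-test rows in Appendices 1 and 2 cover females with reproductive potential, which includes her.
- Pregnancy is a separate exclusion in Section 4.2.

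These safeguards leave a narrow gap. The explicit agreement and the negative serum test, as named entry conditions, appear only in option 4.

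**The case against.** The best reply is that the protocol should be read as a whole. Section 4.1 speaks of an FSH level and does not say that one measurement is enough, so Section 5.3 can be taken as the evidential standard behind option 3. Option 4 is conditional on childbearing potential and can be read as binding any woman who meets Section 5.3's definition. Criterion 2 together with Section 5.3 already makes willingness to use contraception a condition of entry. FSH and serum hCG are also in the same Screening panel, so if they are drawn together an FSH result could not have been used to skip the pregnancy test.

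Much of this stands, and it is why the risk is small. It does not remove the conflict. Option 3 explicitly names women with under 12 months of amenorrhea and no repeat is required, so in ordinary use one Screening value will decide. Option 4's conditional wording sits inside a list where any one item suffices. Criterion 2 is general and does not replace a named agreement.

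Three stronger readings are tempting and are not supported:

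- A reader might infer that such a woman would be free of any contraception duty and would miss her pregnancy tests. The safeguards in Section 5.3, criterion 2, Section 6.6.4.4 and the schedules say otherwise.
- A reader might infer that Section 4.1 declares her non-childbearing. It only makes her eligible; a site would have to draw that conclusion itself.
- A reader might take the under-55 clause to admit menstruating women on FSH alone. It may only say when FSH evidence is needed, and the point does not rest on it.

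**Conclusion.** The inconsistency is real and lies in the current Version 4.0 text. A woman with under 12 months of amenorrhea who is not permanently sterile can be eligible under option 3 while FCBP under Section 5.3, and so can enter without option 4's explicit conditions.

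Its size is small. The protocol gives no count of women who might use the FSH route. Among about 50 planned subjects the number is probably very small and could be zero. Actual harm assumes that a site treats option 3 as settling that she is not FCBP and therefore sets aside the other provisions. The sample size, the significance level and the endpoint analyses are unaffected. This is a low-priority correction, justified because it is nearly free and adopts the standard the sponsor has already written.

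**What to change.** In Section 4.1 and the synopsis:

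1. Delete option 3, or confine it to confirming at least 12 months of amenorrhea in women taking neither hormonal contraception nor hormone replacement. Deletion is cleaner, because the confined form largely overlaps with option 2.
2. State that a woman with under 12 months of amenorrhea who is not surgically sterile must meet option 4.
3. Leave option 1 unchanged. A broader rule sending to option 4 everyone who is not permanently sterile under Section 5.3 could reclassify some women now entering as surgically sterile, because Section 5.3 lists bilateral tube occlusion as a contraceptive method and not among its permanent sterilization methods.

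In Appendices 3 and 4, reword the FSH footnotes to match, so that FSH is no longer called for on the ground of amenorrhea under 12 months. The pregnancy-test rows and the footnotes limiting those tests to FCBP can stay.

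The cost is wording in two places and two footnotes. No procedure is added, since the pregnancy tests are already scheduled, and fewer FSH tests would be needed.

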## 5.4 Dietary Restrictions and Lifestyle Modifications

Throughout the study, subjects will consume the diet associated with their standard of care, maintaining a diet stable in calories and protein intake from Screening through the final study visit.

## 5.5 Other Restrictions

Smoking should be avoided.

Subjects are required to fast (water permitted) for a minimum of 10 hours prior to study drug dosing at Baseline (Visit 2) and EOT/ET (Visit 4) when blood samples will be assessed for biomarkers (APPENDIX 1; APPENDIX 2).

Subjects are required to fast (water permitted) for a minimum of 6 hours prior to the MRS (Cohort A only).

# 6 STUDY ASSESSMENTS AND PROCEDURES (Cohort A and B)

## 6.1 Study Visits

The procedures and assessments for all visits, including Screening, will follow the SOA (APPENDIX 1; APPENDIX 2). Detailed instructions for the procedures and assessments will be provided in the Laboratory Manual.

The study drug should be self-administered at the clinic visit on Day 1 and Day 28 or EOT/ET.

Any impact on the outcomes of this study, including any protocol deviations that result from COVID-19 pandemic or other pandemics or natural disasters, will be discussed in the CSR.

Please note: if allowable measures are included in the protocol, eg, late visits, telephone visits, then it does not need to be a protocol deviation.

## 6.2 Demographics

Age, sex, race, and ethnicity will be recorded for each subject at the Screening Visit. Date of birth will not be recorded.

## 6.3 Medical, Surgical, and Medication Histories

At the Screening Visit, subjects will be interviewed regarding their medical and surgical history and will be recorded in the eCRF. These histories will include past/resolved conditions and active conditions. In addition, the date of last menstrual period will be recorded for female subjects. A medication history will be obtained as part of the medical history. Subjects will be interviewed to provide a list of all prescription medications, over-the-counter medications, and/or dietary supplements (eg, vitamins, herbs, and other dietary supplements) used in the last 4 weeks before the Screening Visit.

## 6.4 Body Measurements

Body measurements to be collected include height and weight, reported in units of kilograms and centimeters, respectively. Height will be measured with the subject’s shoes off. Weight will be measured with the subject’s shoes off and after the bladder has been emptied. Once the subject’s height and weight are entered into the eCRF, the system will compute the BMI.

## 6.5 Laboratory Sample Collections

Blood and urine samples will be collected at the visits indicated in the SOA (APPENDIX 1; APPENDIX 2) for the following assessments:

- Blood collection for local laboratory assessments of safety and tolerability
- Blood and plasma collections for central laboratory assessment of biomarker and other efficacy tests (Cohort A Only)
- Urine collection for the local laboratory assessments of safety and screening

The complete list of analytes to be tested are provided in APPENDIX 3 (Cohort A) and APPENDIX 4 (Cohort B). Detailed instructions for the preparation, handling, and storage of biological samples are provided in the Laboratory Manual.

## 6.6 Safety and Tolerability Assessments

The onset and increase of severity of AEs will be assessed on an ongoing basis. In addition, the safety and tolerability will be monitored by physical examination findings, including body weight; vital signs; and clinical laboratory assessments (chemistry, hematology, and urinalysis).

### 6.6.1 Physical examination

A full physical examination, including a review of all body systems excluding genital examinations, will be performed during Screening to ensure eligibility. Thereafter, a targeted symptom-driven examination can occur based on the occurrence of symptoms (eg, lungs, heart, or based on occurrence of symptoms or AEs).

Physical examination findings will be documented in the subject’s source documents. Any physical examination finding that represents worsening from a baseline condition or clinically significant, as considered by the PI, will be recorded as an AE.

### 6.6.2 Vital signs

Vital signs (sitting systolic and diastolic blood pressure, heart rate, respiratory rate, body temperature, and resting O_2_ saturation) will be measured at each visit except during a telephone visit(s) and recorded in the source documents and eCRF.

The subject should be seated and rested comfortably for at least 5 minutes before obtaining vital signs. Blood pressure may be repeated once to confirm measurement.

Vital signs must be taken before any blood samples are collected at time points where blood is also collected. If possible, vital signs should also be taken before the physical examination is performed, at time points where physical examination is also performed.

### 6.6.3 Echocardiogram

An echocardiogram will be performed at Screening as a criteria for entry into the study. It should rule out significant tricuspid regurgitation, evidence of pulmonary hypertension, or any significant decrease in left ventricular ejection fraction or left ventricle wall abnormality consistent with congestive heart failure.

Note: An echocardiogram is not required to be performed at Screening if documentation of a normal or not clinically significant echocardiogram was performed within 3 months of Screening and after at least 3 months of acute COVID-19 infection. This test is optional depending on the Serum NT-pro BNP test results.

### 6.6.4 Safety laboratory tests

#### 6.6.4.1 Clinical laboratory assessments

Blood and urine samples will be collected for safety and tolerability assessments and will be analyzed at the local laboratory. Procedures for collecting, processing, and handling these samples will be provided in the Laboratory Manual.

The routine clinical laboratory assessments for safety and tolerability include blood sampling for chemistry, hematology, and urine at visits specified in the SOA (APPENDIX 1; APPENDIX 2). The complete list of analytes is provided in APPENDIX 3 (Cohort A) and APPENDIX 4 (Cohort B).

The PI must review the laboratory report, document this review, and record any clinically relevant changes occurring during the study in the AE section of the eCRF. The laboratory reports must be filed with the source documents. Clinically significant abnormal laboratory findings are those that are not associated with the underlying disease, unless judged by the PI to be more severe than expected for the subject’s condition.

If such values do not return to normal, stabilize, or are no longer clinically significant within a period judged reasonable by the PI, the etiology should be identified and the Sponsor should be notified.

A single repeat (retest) per analyte or assessment is allowed during the Screening Period to determine eligibility based on the exclusion criteria and per the PI’s discretion (eg, to recheck laboratory values considered to be out of the typical range for an individual).

All protocol-required laboratory assessments, as defined in APPENDIX 3 (Cohort A) and

APPENDIX 4 (Cohort B), must be conducted in accordance with the Laboratory Manual and the SOA (APPENDIX 1; APPENDIX 2).

